### Sample size calculations and interim analysis

It is anticipated that the average patient with asynchrony who is enrolled into this trial will have 21 VFDs with a standard deviation (SD) of 6 VFDs, based on data from Wit et al. [2]. Considering the impact of improved synchrony on length of MV, we anticipate that NAVA will increase VFDs by 2 days. No patient loss has been considered. We will only analyze patients who are enrolled and randomized. The power analysis has been performed according to Schoenfeld et al. [24]. Thus, the sample size with an alpha of 0.05 and a beta of 0.2 (80 % power) is 153 patients in each group or a total of 306 patients requiring randomization.

Interim analysis will be performed at hospital discharge of the first 102 and 204 randomized patients. If, at the time of these analyses, there is a trend toward better outcome in the control group (*p* < 0.1) the study will be terminated. The study will continue to randomize 306 patients if no adverse impact of the NAVA group is observed. The interim analysis will be performed at the coordinating center (Hospital Universitario [name], Las Palmas de Gran Canaria, Spain) by an independent Data and Safety Monitoring Board (DSMB). It is expected that DSMB meetings will be by conference call and DSMB discussions by email or conference call.

All adverse events reported will be sent to the DSMB as well as to the IRB for review (see Additional file 4). All serious events will be sent within 24 h after being received by the coordinating center. Nonserious events will be sent within 1 week of reception by the coordinating center. All unexpected, and related or possibly related, adverse events will be reported to the DSMB and the IRB. The DSMB will review the overall status of the study: number of patients enrolled overall and in each center, adherence to the protocol overall and by each center.

### Data analysis

Data will be collected in each participating ICU using a standardized form. Data will be transmitted to the coordinating center whenever a patient dies or is discharged from the hospital. Before exporting the data into a computerized data base at the coordinating center, a trained data collector from the coordinating center will check the completeness and the quality of information. Logical checks will be performed for missing data and to find inconsistencies, especially regarding clinical diagnosis, date, and ventilatory parameters. If necessary, the data collector will contact the investigator by phone to validate the data or reformat the data for entry into the database.

Descriptive statistics will be expressed as mean ± SD or median and interquartile range depending on the nature and distribution of the variables. Inferential statistics will use estimates of the mean of the differences and their 95 % confidence intervals (CI). Variables normally distributed will be compared with the Student’s *t* test. For variables without a normal distribution, the Mann-Whitney *U* rank test will be used for comparison. Categorical variables will be compared using Fisher’s exact test. The primary outcome variable (number of VFDs) will be assessed with the Student’s *t* test or the Mann-Whitney *U* rank test dependent on the distribution of the data. The relative risks and their 95 % CIs will be estimated. For all these comparisons, we will consider a difference to be statistically significant if *p* < 0.05.

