### Study design

This study is a prospective, multicenter, randomized controlled, clinical trial in 306 adult patients (male and female) with ARF admitted to a network of 18 ICUs from university and community hospitals in Spain (Appendix 1).

The trial has been designed in accordance with the fundamental principles established in the Declaration of Helsinki, the Convention of the European Council related to human rights and biomedicine, and the Universal Declaration of UNESCO on the human genome and human rights, and within the requirements established by the Spanish legislation (Law 14/2007, Law 15/1999) in the field of biomedical research, the protection of personal data, and bioethics. The study was registered on 15 November 2012 at https://clinicaltrials.gov/ct2/show/NCT01730794 with the identification number NCT01730794. The study was approved by a referral Ethics Committee (Hospital Clínico Universitario de Valencia, Valencia, Spain) and the Institutional Review Boards (IRBs) of all participating hospitals (Additional file 1). For inclusion into the study, signed written informed consent from the patient or the patient’s personal legal representative will be obtained (Additional file 2). See Additional file 3 for the Standard Protocol Items: Recommendations for Interventional Trials (SPIRIT) checklist of the study protocol.

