**Fig. 1 Fig1:**
[figure not shown]
Study design diagram

The randomization list was done by the statistician of the study ([name]), according to a computer-generated random number table based on a 1:1 allocation. This list was generated when the investigators and all Ethics Committees and IRBs of the participating centers had approved the study design. Randomization is stratified by center to ensure an equal distribution of patients in each arm by each ICU. Patients are randomly allocated to the two arms of the study (NAVA or no NAVA) by the clinical investigator in each participating ICU according to the precise written allocation contained inside a prenumbered, opaque, sealed envelope sent in blocks of ten envelopes to each participating ICU. Investigators must respect the numerical sequence of the envelopes. Only two members of the Trial Management Team have access to the randomization list: the project manager and the statistician. They keep the randomization list in their private office at the Research Unit of the Coordinating Center. The coordinating center does not enroll patients.

Our study characteristics do not allow the blinding of investigators to the intervention being tested. Once a participating ICU randomizes a patient, their investigators must contact the project manager of the study to inform and confirm the randomization number, the correct sequence of the prenumbered envelope, and the intervention arm. Screening, enrollment, randomization, treatment initiation, and follow-up of randomized patients is performed by the investigators and attending physicians in each participating ICU. Subsequent blocks of ten envelopes are sent to those participating ICUs with high enrollment rates. Participating clinicians do not know whether the pattern of stratification by center is for every 10, 20, or more envelopes during the study period.

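### Randomization is stratified by ICU but the stated primary test ignores ICU, so the interval for ventilator-free days is slightly too wide if ICUs differ

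*Protocol article*

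**What the plan says.** Under Enrollment into the study and randomization, the article says: "Randomization is stratified by center to ensure an equal distribution of patients in each arm by each ICU". Allocation is 1:1, and numbered sealed envelopes go to each ICU in tens. Under Study design, patients are "admitted to a network of 18 ICUs from university and community hospitals in Spain".

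Under Data analysis, the primary comparison is fixed: "The primary outcome variable (number of VFDs) will be assessed with the" Student's t test or the Mann-Whitney U test, according to the observed distribution. Effects are to be reported as mean differences with 95% confidence intervals. The article describes no stratified, center-adjusted or covariate-adjusted analysis of VFDs.

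The sample size section assumes that the average patient "will have 21 VFDs with a standard deviation (SD) of 6 VFDs" and adds: "we anticipate that NAVA will increase VFDs by 2 days". With "sample size with an alpha of 0.05 and a beta of 0.2" it arrives at 153 per arm, 306 in total. It includes no term for center.

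**The concern.** When arms are balanced within centers, a center with generally high or low VFDs contributes about equally to both arms, so its effect largely cancels from the difference. The real sampling variance of the difference then contains only within-center variation. A two-sample t or Mann-Whitney test does not know this and counts between-center variation as error.

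Some variation between ICUs is plausible from the text. University and community units are mixed, the control mode is chosen from five by the treating team, and the sedative regimen follows the physician and the unit. Center is also the only stratification factor the article names. At stake is precision that the design has already secured and the stated analysis gives away.

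**Working it through.** **Inputs.** From the sample size section: difference δ = 2, SD σ = 6, n = 153 per arm, α = 0.05 (taken as two-sided, since sidedness is not stated). From Study design: 18 ICUs, so 306/18 = 17 patients each if they recruit equally (assumed). The ICC ρ, the share of VFD variance lying between ICUs, is not in the article and is varied from 0 to 20%. The SD of 6 is treated as the total SD.

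**The plan's own figure.** n = 2[σ(1.96 + 0.842)/δ]² = 2(8.405)² = 141.3, so 142 per arm, not 153. With 153 per arm, SE = 6√(2/153) = 0.686 and power = Φ(2/0.686 − 1.96) = 83.0%. The article cites a power method specific to VFDs that is not shown, so 153 is not called wrong. The gap does not affect this point.

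**Formulas, with balance within ICUs.**
- Standard error used by the planned t test: σ√(2/n) = 0.686.
- Actual standard error: 0.686√(1 − ρ).
- Excess interval width: 1/√(1 − ρ) − 1.
- Type I error of the planned test: 2[1 − Φ(1.96/√(1 − ρ))].
- Power of the planned test: Φ[(2 − 1.96 × 0.686)/(0.686√(1 − ρ))].
- Power with center in the model: Φ[2/(0.686√(1 − ρ)) − 1.96].

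| Assumed ICC | Actual SE | Interval too wide by | Type I error, planned | Power, planned | Power, center-adjusted |
|---|---|---|---|---|---|
| 0 | 0.686 | 0 | 5.0% | 83.0% | 83.0% |
| 1% | 0.683 | 0.5% | 4.9% | 83.2% | 83.4% |
| 2% | 0.679 | 1.0% | 4.8% | 83.3% | 83.8% |
| 5% | 0.669 | 2.6% | 4.4% | 83.7% | 84.9% |
| 10% | 0.651 | 5.4% | 3.9% | 84.3% | 86.7% |
| 20% | 0.614 | 11.8% | 2.8% | 85.7% | 90.3% |

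**Simulation check.** This used 18 ICUs of 17 patients, permuted blocks of ten within ICU, normal data and 4,000 trials per setting. The adjusted model had fixed center effects.
- ICC 2%: power 83.6% (t test) against 83.8% (adjusted).
- ICC 5%: 83.6% against 84.2%; t-test type I error 4.1%.
- ICC 10%: 84.3% against 86.9%; type I error 4.3%.
- ICC 20%: 84.5% against 89.4%; type I error 3.8%.

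A second simulation at ICC 5%, 10% and 15% gave t-test power of 82.6%, 85.5% and 84.8%, against 83.9%, 86.8% and 88.3% adjusted, with t-test type I error of 4.7%, 4.0% and 3.9%. Monte Carlo standard errors at 4,000 trials are about 0.3 points for type I error and 0.6 for power. Direction and approximate size agree with the formulas.

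**Which adjusted method.** The van Elteren test, the center-stratified rank test, was simulated separately (3,000 trials, equal centers). Power for Mann-Whitney against van Elteren was 80.6% and 79.3% at ICC 2%, 81.4% and 80.4% at 5%, 82.6% and 82.8% at 10%, and 82.8% and 84.9% at 15%. It shows no gain at ICC 5% or below and practically none at 10%, so the gain in the table belongs to the linear model.

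**The case against.** The strongest reply is that nothing becomes invalid. The planned test holds its type I error at or below 5%, exceeds the stated 80% power on the article's own inputs, and loses almost nothing if ICUs differ little. No ICC is given, so the loss cannot be fixed at any one value. All of that stands and limits the point to a modest one.

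It could also be said that adjustment belongs in an analysis plan that is not shown. For optional covariates that is fair. It does not cover center, because the article names the primary test and that test does not match the allocation described earlier in the same article.

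Four stronger readings might be inferred and are not supported:
- **The trial is underpowered.** On the stated difference, SD and group size, the unadjusted t test has about 83% power.
- **Leaving out baseline makes the interval wrong.** Baseline variables were not used to stratify. Omitting them costs efficiency, but the unadjusted interval remains correct with respect to them.
- **Weaning is left to local practice, so large center effects must be expected.** The article sets readiness criteria, duration and failure criteria for spontaneous breathing trials, calls for extubation after success unless there is a documented reason, and gives criteria for noninvasive ventilation after extubation. Some latitude remains, but weaning is largely protocolized.
- **A baseline severity score can be added without new data.** Table 1 lists none. The APACHE II score named under Ventilatory management is taken on the day of extubation, after randomization.

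**Conclusion.** The mismatch is real and small. Allocation is stratified by ICU and the stated primary test is not. If ICUs differ in VFDs, the interval is too wide by about 0.5% at an assumed ICC of 1% and about 5% at 10%. The corresponding power loss runs from about 0.2 to 2.4 points. At an ICC of 2% or below it is negligible; larger losses need an ICC above 10%, which nothing in the article establishes.

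These figures rest on the stated SD of 6 and difference of 2, normal data, equal ICU sizes, and balance within each block of ten. The article does not confirm that last assumption, since it keeps the balancing interval from clinicians. VFDs are bounded and set to 0 for deaths, and a skewed distribution of that kind was not simulated.

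**What to change.** In Data analysis, make the primary estimate the mean difference in VFDs, with its 95% confidence interval, from a linear model containing arm and center. Enter center as a random effect, or pool small centers by a rule fixed in advance, and use a heteroscedasticity-robust standard error. This keeps the mean difference that the article already intends to report.

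Days ventilated before randomization may be added as a prespecified covariate. They are fixed before allocation and count directly against VFDs when these are measured from intubation. The reason to add them is precision alone. Include a baseline severity score only if one is already collected.

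Keep the unadjusted t or Mann-Whitney test, or the van Elteren test, as a sensitivity analysis. The cost is a change of wording before the data are analysed: no extra patients, and no data beyond center and intubation and randomization times.

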## Discussion

Assisted MV is a highly complex process that requires an intimate interaction between the ventilator and the patient [25]. The complexity of the interaction between the ventilator and the patient with ARF is frequently underappreciated by the bedside clinician. The pattern of gas delivery by the ventilator and the patient’s own breathing pattern must match almost perfectly to avoid asynchrony between the patient and the ventilator. To date, we have no direct evidence that improving patient-ventilator synchrony improves patient outcome. However, there is growing evidence that asynchronies negatively correlate with clinical outcomes, including prolonged MV and ICU length of stay [1, 2] and lead to higher mortality [3].

NAVA is a newer mode for managing patients with ARF under MV. The insertion of the NAVA catheter is similar to the insertion of a nasogastric feeding tube and it is not associated with any additional risks. Patients with ARF who are able to breathe spontaneously while they are receiving MV are required to follow the lead of the ventilator and to adjust their respiratory center output to match the way the clinician sets the ventilator, otherwise, asynchrony will occur. Currently, it has become more accepted that the respiratory center of the patient in most circumstances is the most appropriate determinant of ventilatory pattern as a result of the increased recognition of the negative outcomes associated with patient-ventilator asynchrony [3]. In a recent study, Yonis et al. [26] reported reduced asynchrony during assisted ventilation with NAVA as compared to pressure support ventilation in 30 patients with respiratory failure who were randomly assigned to 23 h of pressure support ventilation and 23 h of NAVA. Also, in a previous study [27], we reported that NAVA, as compared to pressure support ventilation, resulted in improved synchrony, reduced ventilatory drive, increased breath-to-breath mechanical variability and improved patient comfort in 12 mechanically ventilated pediatric critically ill patients. In a series of 11 patients recovering from ARF, NAVA provided better patient-ventilator interaction [28]. In a recent study in 25 patients previously ventilated with controlled MV for at least 72 h who were randomized to be ventilated for 48 h with pressure support ventilation (*n* = 12) or NAVA (*n* = 13), NAVA improved diaphragmatic efficiency whereas pressure support ventilation did not [29].

Since NAVA does not control the patient’s ventilatory pattern, the patient is allowed to select whatever pattern the respiratory center considers appropriate. Neither pressure, flow, volume nor time is set by this novel ventilatory modality of assisted MV. All that is set during NAVA is the proportion of effort provided by the ventilator to supplement the patient’s own effort. In other words, NAVA follow the lead of the patient but does not force a ventilatory pattern on them [25]. If our hypothesis is correct, the introduction of NAVA into the routine care of adult patients with ARF will have a marked impact on the duration of MV, length of stay in critical care units, and health care costs. If our hypothesis is true, NAVA will become the preferred mode of assisted MV in patients spontaneously breathing with ARF.

### Trial status

The first patient was enrolled on 28 March 2014. The expected duration of the study is 50 months.

### Trial organization

The study principal investigators who contributed to the study design and approved the final protocol constitute the Steering Committee (Appendix 2). The Executive Committee comprises the main investigators of each participating center and is responsible for administrative, trial, and data management. The Data and Safety Monitoring Board is composed of three external, independent experts in critical care medicine, mechanical ventilation and ARDS and, with the general data provided by three internal members, it will recommend the continuation or discontinuation of the trial based on the data from the interim analysis. The Trial Management Team comprises a chief investigator, a project manager, a statistician, a clinical epidemiologist, and an investigator expert in clinical trials. The responsibilities of this team are:Planning and conducting the study: designing the protocol, Case Report Forms, designing the investigator manual, and managing and controlling the data qualityResearch center support: assisting the centers with the administrative submission, monitoring recruitment rates, providing sealed randomization envelopes, taking actions to increase patient enrollment, monitoring follow-up, auditing, and sending study materials to the research centersProducing a monthly study newsletter (*Navanews*)Programming a Research-in-Progress meeting at least once every year with the principal investigators from all sitesStatistical analysis and research reporting: interim and complete statistical analysis and helping to write the final manuscript

## Appendix 1

## Abbreviations

AI: Asynchrony index
ARDS: Acute respiratory distress syndrome
ARF: Acute respiratory failure
COPD: Chronic obstructive pulmonary disease
DSMB: Data and Safety Monitoring Board
Edi: Electrical activity of the diaphragm
ICU: Intensive care unit
MDI: Metered-dose inhaler
MV: Mechanical ventilation
NAVA: Neurally Adjusted Ventilatory Assist
PaCO_2_: Partial pressure of carbon dioxide
PaO_2_/FiO_2_: Ratio between partial pressure of oxygen in arterial blood and fraction of inspired oxygen
PBW: Predicted body weight
PEEP: Positive end-expiratory pressure
PRVC: Pressure-regulated volume control
PS: Pressure support
SBT: Spontaneous breathing trial
SOFA: Sequential organ failure assessment
SpO_2_: Peripheral capillary oxygen saturation
VFD: Ventilator-free days
VS: Volume support
VT: Tidal volume
